## Abstract

**Introduction:**

Knee osteoarthritis (KOA) is a major cause of disability, and both external Chinese herbal therapy (ECHT) and pulsed electromagnetic field (PEMF) therapy have shown potential in managing KOA symptoms. However, no research has directly compared the efficacy of ECHT, PEMF, and their combined use on pain relief and functional improvement in older adults with KOA. This highlights a significant research opportunity to explore the comparative benefits of these treatment modalities.

**Methods and analysis:**

This randomized controlled trial (RCT) aims to enroll 124 older adults with KOA and will randomly allocate them across four treatment groups: (1) exercise with health education, (2) exercise with ECHT, (3) exercise with PEMF therapy, and (4) exercise with a combination of ECHT and PEMF. Each intervention will be administered five times per week for 4 weeks. The primary endpoints are pain and functional capacity, while secondary measures encompass lower limb range of motion, alignment, joint space, and serum cytokine levels. Assessments will be conducted at baseline, post-intervention, and at the 4-week follow-up.

**Discussion:**

This trial is poised to conduct a thorough comparative analysis of the impacts of ECHT, PEMF therapy, and their combined application in older adults with KOA. The study findings will not only inform clinical practice by offering data-driven recommendations but also enrich the scientific discourse on the complex interplay between inflammation, pain, and function in KOA.

**Clinical trial registration:**

Chinese clinical trial registry platform: www.chictr.org.cn (no. ChiCTR2400087644).

## Introduction

Knee osteoarthritis (KOA) stands as the world’s most prevalent musculoskeletal disorder and a leading cause of disability, affecting millions globally (1). Common symptoms of KOA include pain, stiffness, and impaired functionality, significantly impacting the quality of life (2).

KOA affects the entire joint architecture, which leads to structural changes across multiple components: hyaline articular cartilage, subchondral bone, ligaments, joint capsule, synovium, and periarticular muscles, reflecting its complexity (3, 4). The intricate pathogenesis of KOA is influenced by a confluence of factors—mechanical, inflammatory, and metabolic—that culminate in the deterioration and eventual failure of the synovial joint, perpetuating a detrimental cycle.

The personal, social, and economic toll of KOA is extensively documented, underscoring the pressing need for precise and efficacious therapeutic interventions to mitigate these burdens (5, 6). Despite significant strides in our comprehension of KOA, the development of impactful treatments remains a formidable challenge (7, 8). The current armamentarium for KOA management spans a diverse array of strategies, including non-pharmacological interventions, pharmacological therapies, and surgical interventions (9). The overarching objectives of these treatments are to alleviate symptoms and to slow the progression of the disease.

Clinical guidelines prioritize first-line treatments that encompass patient education, self-management strategies, regular exercise, weight management for overweight individuals, and physical therapy (10, 11). Although pharmacotherapy can provide symptomatic relief for KOA, the potential for adverse effects can limit the widespread use of these medications, highlighting the imperative for continuous research into safer and more tolerable treatment options (12, 13). It is essential to explore innovative approaches that can enhance the therapeutic landscape for KOA, ensuring that patients have access to treatments that are both effective and safe.

The escalating apprehensions regarding the safety profiles and economic implications of conventional KOA treatments have spurred a burgeoning interest in the exploration of natural remedies as credible alternatives. This shift is further compounded by the enduring challenge of managing the chronic pain associated with KOA, which has led to an intensified investigation into the potential of herbal therapies as viable solutions (8).

The exploration of herbal remedies in the treatment of KOA has unveiled innovative therapeutic pathways, offering fresh perspectives on managing this complex condition (14, 15). Among these, the topical external Chinese herbal therapy (ECHT) has risen to prominence, capturing the interest of both patients and healthcare providers due to its unique approach to KOA management (16).

ECHT’s initial indications of efficacy are promising, yet they underscore the necessity for a more profound and methodical investigation. To solidify its place within the KOA therapeutic framework, ECHT requires extensive research and well-designed clinical trials. These studies should not only validate its safety and effectiveness but also delve into the intricate biological mechanisms that confer its therapeutic benefits.

By understanding how ECHT interacts with the body’s systems and influences the disease process, researchers can refine its application, potentially enhancing its efficacy and safety profile. This meticulous scientific exploration is vital for establishing ECHT as a reliable and evidence-based component of KOA treatment strategies. It will also empower healthcare providers to make informed decisions when recommending ECHT to patients, ensuring that they can do so with a clear understanding of its potential benefits and any associated risks.

On the other hand, pulsed electromagnetic field (PEMF) therapy has gained attention as a simple, safe, and noninvasive treatment option for KOA (17). Its appeal lies in its potential to stimulate bone and cartilage repair, offering relief from pain and stiffness (18, 19). Recent guidelines have acknowledged PEMF’s therapeutic value; however, the endorsement is cautiously moderate due to the relatively short-term follow-ups in the existing body of research. There is an evident requirement for long-term studies to confirm and expand upon PEMF’s therapeutic potential (20).

Furthermore, the pathogenesis of KOA involves a complex interplay of factors. Current research indicates that joint stress injuries and apoptosis contribute to the degeneration of articular cartilage, while an imbalance in chondrocyte synthetic metabolism can lead to abnormal immune responses, which are central to the disease’s progression (21). Experimental studies have identified key players in this process, such as interleukin (IL)-1 and matrix metalloproteinase (MMP), which significantly influence the development and worsening of KOA (22).

When the knee joint cartilage sustains damage, the release of pro-inflammatory cytokines, including tumor necrosis factor (TNF-*α*), IL-1, IL-6, and nitric oxide (NO), into the synovial fluid initiates local inflammatory responses (21). This inflammatory activation triggers multiple signaling pathways, leading to the production of matrix metalloproteinase-3 (MMP-3) and inducible nitric oxide synthase (iNOS). The ensuing imbalance between matrix metalloproteins (MMPs) and tissue inhibitors of metalloproteinases (TIMPs) disrupts the delicate equilibrium within the articular cartilage (23). This disruption compromises chondrocyte function and the structural integrity of the extracellular matrix, hastening the degradation of the cartilage matrix and thus contributing to the initiation and progression of OA. Understanding these intricate mechanisms is crucial for developing targeted therapies that can address the root causes of KOA, potentially halting or even reversing the disease’s progression. As research continues to unravel the complexities of KOA pathogenesis, the hope is to identify more effective interventions that can improve patient outcomes and quality of life.

Our comprehensive review of the literature reveals a significant gap in studies examining the synergistic effects of ECHT and PEMF therapy on pain reduction and functional improvement in elderly KOA patients. The objective of this study is to address this research gap by investigating the impacts of ECHT therapy, PEMF therapy, and their combined application on pain alleviation, functional enhancement, and molecular changes in older adults with KOA. This study aims to investigate the individual and combined effects of ECHT and PEMF therapies on pain alleviation and functional improvement in older adults with KOA and gather evidence that elucidates the underlying molecular mechanisms at play, providing a deeper understanding of how these therapies influence the disease’s progression at a molecular level.

We hypothesize that ECHT and PEMF therapies will each induce distinct improvements in pain and functionality, as well as varying molecular responses in older adults with KOA. We anticipate that the combined application of both therapies will result in more pronounced molecular changes, potentially leading to superior therapeutic outcomes compared to either treatment alone.

This research is poised to contribute valuable insights into the comparative efficacy of these therapies and their potential synergistic effects, thereby informing more personalized and effective treatment strategies for older adults suffering from KOA.

## Methods and analysis

### Study design

This will be a prospective, single-blinded, parallel-armed, randomized controlled trial (RCT). Participants will be allocated to one of the four groups: (1) exercise and health education group, (2) ECHT therapy + exercise group, (3) PEMF therapy + exercise group, or (4) ECHT + PEMF therapy + exercise group. The checklist of Standard Protocol Items: Recommendations for Interventional Trials (SPIRIT) is provided in Appendix 1, while the SPIRIT schedule is presented in Figure 1. Figure 2 illustrates the flowchart detailing the progression of the trial’s methodology.

**Figure 1 fig1:**
[figure not shown]
Schedule of enrolment, interventions, and assessments. EATCH, The external application of traditional Chinese herbs; PEMF, pulsed electromagnetic field; VAS, visual analogue scale; WOMAC, The Western Ontario and McMaster Universities Osteoarthritis Index (Likert version 3.11).

**Figure 2 fig2:**
[figure not shown]
Study flowchart of the research process according to the randomized trial synthesis criteria. ECHT, external Chinese herbal therapy; PEMF, pulsed electromagnetic field.

To explore the molecular mechanisms of ECHT, PEMF, and their combined therapy in older adults with KOA, this study will employ molecular biological techniques to analyze the following aspects:

Assessment of inflammatory markers: enzyme-linked immunosorbent Assay (ELISA) will be employed to meticulously measure variations in the serum levels of key inflammatory response factors. Specifically, it detects alterations in C-reactive protein (CRP), high-sensitivity C-reactive protein (hs-CRP), TNF-*α*, and interleukin-6 (IL-6), providing a quantitative assessment of the inflammatory state in patients with KOA (24).

Exploration of inflammatory pathways: a multifaceted approach will be utilized to investigate the intricate mechanisms of inflammation in KOA.

Immunoturbidimetry: this technique will be applied to quantify the serum levels of Matrix Metalloproteinase-3 (MMP-3), Matrix Metalloproteinase-13 (MMP-13), and hyaluronic acid (HA), which are pivotal in the degradation of cartilage (25).

Colorimetric methods: these will be employed to assess the serum content of NO, and malondialdehyde (MDA), offering insights into oxidative stress and the body’s antioxidant defenses.

ELISA: Will be further utilized to gauge the levels of Interleukin-1 beta (IL-1β), prostaglandin E2 (PGE-2), and IL-1, which are critical mediators of the inflammatory response in KOA (26).

### Participants

Participants will be recruited from The Second People’s Hospital of Kunming, and Yan’an Hospital of Kunming City. The trial was registered in the www.chictr.org.cn (ChiCTR2400087644), and will be conducted in accordance with the Declaration of Helsinki. All participants will provide written informed consent before data collection. The trial has begun on July 22, 2024, and will be end on May 30, 2025.

The inclusion criteria are as follows: (1) aged between 60 and 80 years old; (2) a diagnosis of KOA in at least one knee, confirmed by the American College of Rheumatology’s clinical criteria; (3) a Kellgren-Lawrence (K-L) radiographic grade of 2 or higher. Exclusion criteria included: (1) the presence of a neurodegenerative or neurosensory disorder affecting the knee, distinct from KOA; (2) a history of lower extremity joint trauma within the last 3 months; (3) a scheduled total knee replacement in the upcoming months; (4) a documented allergy to traditional Chinese herbs; (5) prior treatment for KOA with steroids, intra-articular injections, or other analgesics within the past 3 months; (6) concomitant other physical therapies.

### Randomization and blinding

The random allocation sequence will be generated by an online generator (https://www.random.org). The allocation sequence will be kept in a sealed, opaque envelope. The principal investigator will assign participants to the respective intervention groups. The allocation will be blinded to the outcome assessors and the data analyst. Participants will be instructed not to disclose the allocation to the outcome assessors.

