### Outcome measures

All demographic information (e.g., age, gender and affected side, etc.) will be collected at baseline assessment session. All outcome assessments will be performed by a blinded assessor in each hospital on three occasions, i.e., at baseline, within 1-week after the completion of intervention, and at a 4-week follow-up.

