### Sample size

GPower 3.1 software (Heinrich-Heine-Universitat, Dusseldorf, Germany) was used to estimate the sample size. Wang et al. (36) 8-week traditional Chinese herbs hot compress (TCHHC) trial demonstrated a significant interaction on the total WOMAC score between the TCHHC combined with therapeutic exercise group and the therapeutic exercise alone group, yielding a partial eta-squared (
$\eta_{p}^{2}$
) of 0.148, corresponding to an effect size of *f* = 0.416 (36). A conservative approach was adopted for our sample size estimation, considering the comparison of two distinct treatment factors—ECHT and PEMF—and their combined application, alongside a reduced intervention duration of 4 weeks. Employing a 4 (group factor) × 3 (time factor) RM ANOVA framework, and assuming a small effect size (*f* = 0.15), a significance level (*α*) of 0.05, statistical power of 0.80, and accounting for a 15% attrition rate, the total sample size required was 124 participants, evenly distributed across the four groups, i.e., 31 in each group. The sample size is expanded by 10% compared to the original registration in the Chinese Clinical Trial Registry. This modification was necessitated by a post-initiation adjustment to the attrition rate assumption, which was revised upward to a more conservative 15% based on emerging data from the ongoing trial.

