### Statistical analysis

Data entry will be performed by two independent researchers so that the accuracy of the input data can be cross-checked. The Statistical Package for Social Sciences (SPSS) version 26 will be used to conduct the data analysis. Intention-to-treat analysis will be performed. The normality of the data will be checked using the Shapiro–Wilk test. To compare the baseline characteristics of the four groups, one-way ANOVA (or its nonparametric equivalent: Kruskal–Wallis test) or Chi-square tests will be used, depending on whether the criteria for parametric statistics are fulfilled. Those relevant variables that show important between-group differences will be entered as covariates for subsequent analysis. To compare the treatment effects of the 4 intervention approaches, multivariate 4 × 3 ANOVA or ANCOVA with repeated measures (mixed design; repeated factor: time; between-subject factor: group) will be used to determine the time effect and treatment × time interaction effect for each outcome variable of interest. The Greenhouse–Geisser correction will be applied if the assumption of sphericity is violated. If significant results are found, *post-hoc* multiple comparisons of group effects and contrast analyses of time effects will be performed. Bonferroni adjustment will be performed in *post-hoc* analysis to account for the increased risk of Type I errors associated with multiple comparisons. If the criteria for parametric statistics are not fulfilled, the Mann–Whitney test and Wilcoxon test will be used.

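### Hospital is not a pre-specified factor in the analysis of this two-hospital trial; it could enter only through a baseline-difference rule, at a modest cost in precision

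*Protocol article*

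**What the plan says.** The Participants section names two recruiting hospitals, and Table 1 places treatment in a physical therapy room at each. Outcome measures states: "All outcome assessments will be performed by a blinded assessor in each hospital on three occasions".

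On allocation, Randomization and blinding says "The random allocation sequence will be generated by an online generator" and "The allocation sequence will be kept in a sealed, opaque envelope". It neither describes stratification or blocking by hospital nor rules them out. Sample size plans 124 participants, "evenly distributed across the four groups, i.e., 31 in each group".

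The Statistical analysis section lists the factors of the model: "mixed design; repeated factor: time; between-subject factor: group". Hospital is not among them. Other variables can enter through one rule: "Those relevant variables that show important between-group differences will be entered as covariates for subsequent analysis". If significant results are found, post-hoc comparisons of groups follow. If parametric criteria fail, Mann–Whitney and Wilcoxon tests replace the model.

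**The concern.** Hospital is a known source of variation before the first participant is randomised. Patient mix may differ between the hospitals, and exercise is supervised and tailored on site. The manual muscle test and goniometer range of motion also depend on who measures. A factor known in advance is best put into the model in advance. Here the factors are listed and hospital is not one of them, so its inclusion would be decided after looking at the data.

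What is at stake is precision and protection against an unlucky allocation. Hospital differences in change go into the error term of the group × time test. Hospital differences in level go into the error of any post-hoc group comparison that is not adjusted for baseline. If the arms differ by chance in hospital share, nothing in the stated model corrects for it.

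**Working it through.** **Inputs from the article.** 124 participants, 31 per arm, 4 groups, 3 occasions, f = 0.15, α = 0.05, power 0.80, 15% attrition, and a minimum clinically important difference of 1.8 cited for pain. **Assumptions, not in the article.** Correlation between occasions ρ = 0.5 and sphericity; a 62:62 split by hospital (other splits shown); unstratified allocation; hospital differences g of 0.3, 0.5 and 0.8 SD.

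**1. The plan's own figure, and the cost of the extra term.** For the group × time test, λ = f²·N·m/(1 − ρ) = 0.0225 × 105 × 3/0.5 = 14.175, with df1 = 3 × 2 = 6 and df2 = (105 − 4) × 2 = 202. Power is 0.804 (N = 104 gives 0.799). Then 105/0.85 = 123.5, rounded up to 124, so the stated total is reproduced. (With ρ = 0.3 it would be 171, with ρ = 0.7 it would be 76.) Adding hospital and hospital × time makes df2 = (105 − 5) × 2 = 200, and power is still 0.804. The total stays at 124.

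**2. Chance imbalance.** With hospital share p, the SD of the difference in share between two arms of 31 is √[p(1 − p) × (124/123) × (2/31)]. For p = 0.5 this is √(0.25 × 1.008 × 0.0645) = 0.128, or 12.8 percentage points. Simulated allocations agree:

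| Split | SD of a pairwise gap | Pairwise gap ≥ 20 points | Median of the largest gap among four arms |
|---|---|---|---|
| 50:50 | 12.8 points | 10% | 19 points |
| 70:30 | 11.6 points | 7% | 16 points |

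The mean gap is zero, which is why the estimate is unbiased.

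**3. Shift of a contrast.** The shift is the gap in share times the hospital difference. With g = 0.5 SD its SD is 0.5 × 0.128 = 0.064 SD units. If the hospitals differed by 1 VAS point in change (an assumption), the SD for a given pair of arms would be 0.13 points. The most different pair would typically be off by 0.19 points, about 11% of 1.8.

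**4. Precision.** With a 62:62 split, leaving hospital out raises the residual variance from 1 to 1 + g²/4: 1.0225, 1.0625 and 1.16 for the three values of g. The table gives the simulated power of a two-arm contrast on one score without baseline adjustment. There were 4,000 runs per cell, with simulation error about √(0.8 × 0.2/4000) = 0.006. The true difference is 0.72 SD, chosen to give about 0.80 when g = 0.

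| g | Hospital omitted | Hospital included |
|---|---|---|
| 0.3 SD | 0.797 | 0.804 |
| 0.5 SD | 0.777 | 0.799 |
| 0.8 SD | 0.754 | 0.802 |

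The loss is 0.7, 2.2 and 4.8 points. Type I error with hospital omitted was 0.041 to 0.053.

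**5. What reaches the planned test.** A group × time comparison between two occasions is a comparison of change scores. An offset that is the same at all occasions drops out of every change score. The losses in step 4 therefore apply to post-hoc comparisons of level. They apply to the interaction only if g is read as a hospital difference in change, in SDs of change.

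**6. The covariate rule as a safeguard.** Suppose an important difference is judged by the section's own baseline chi-square test at the 5% level. In 40,000 allocations with a 62:62 split, hospital was flagged in 5%. Among the roughly half in which the largest gap was 6 of 31 or more (19 points), it was flagged in about 10%. Most sizeable imbalances would go unadjusted.

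**7. If allocation was in fact stratified.** The simulation with stratified allocation and g = 0.8 SD gave power 0.730 without and 0.800 with the hospital term, and type I error 0.035 and 0.047. A small part of that power loss comes from a fixed remainder of one participant per arm in the simulation, a shift of 0.8/31 = 0.026 SD. The rest arises because a model that ignores the stratum overstates the standard error.

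**The case against.** Much of the case on the other side stands.

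- A reader might infer that a single unstratified list serves both hospitals. The article does not say so. The singular wording is ordinary, and an article commonly leaves stratification and blocking to the full protocol. No finding about the list, and no call for new lists, can rest on that silence.
- A reader might also infer that assessor and site differences pass systematically into the arm comparisons. They do not. Imbalance under randomisation is chance, the mean shift is zero, and type I error is held. If each hospital's assessor scores all three occasions, a constant offset cancels from the planned interaction.
- Both primary outcomes, VAS pain and WOMAC, are patient-reported. Assessor differences bear chiefly on muscle strength and range of motion, which are secondary.
- Hospital is not excluded, since the covariate rule could admit it.
- The article does not state that therapists differ by hospital. Supply of the herbs by one hospital points to a common product.

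Two things remain. Post-hoc group comparisons of level, and the Mann–Whitney fallback if applied to levels, do not remove an offset; hospital differences in change do not cancel anywhere. And a rule that admits hospital only after a baseline comparison is no substitute for naming it in advance.

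**Conclusion.** The point holds as a minor one about the stated model: a known design feature is left to a data-driven rule. The harm is lost precision and uncorrected chance imbalance, not bias or an inflated type I error. Its size is a pairwise SD of about 13 percentage points in hospital share (62:62 split and unstratified allocation assumed). The power cost is about 1 to 5 points for assumed hospital differences of 0.3 to 0.8 SD. That power figure is for a single score without baseline adjustment, so it overstates what a constant offset costs the group × time test, where the cost is nil. The documents give neither the recruitment split nor any hospital difference, so the actual loss could lie below this range. The recommendation does not depend on how the list was made: without stratification the term recovers precision, and with it the term is needed to match the design.

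**What to change.** In the Statistical analysis section, name hospital as a fixed between-subject factor, together with its hospital × time term, for every outcome and regardless of baseline tests. The hospital × time term is the part that removes site differences in change. No group × hospital term is needed for this purpose. Where the rank-based fallback is used, stratify it by hospital, because a plain Mann–Whitney test cannot carry the term. State in Randomization and blinding whether allocation was stratified by hospital.

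The cost is one between-subject degree of freedom (df2 from 202 to 200 in the interaction test) and slightly more analysis work. The sample size does not change, and the model change needs nothing from participants, so it can still be made before the data are analysed.
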